#### 1.1.2 Rationale for the proposed study

##### ***Prednisolone***

Reducing antibiotic use is crucial to lowering the risk of antibiotic resistance. One of the methods is to use an alternative treatment that does not involve antibiotics. The current alternative treatments (i.e. ear drops, herbal products, probiotics, zinc, decongestants) demonstrate insufficient evidence on their benefits for AOM [15,16]. It is important to understand the pathophysiology of AOM, which is an inflammatory process involving both cellular and chemical inflammatory mediators (i.e. cytokines, chemokines, mast cells, prostaglandins, leukotrienes) in the middle ear. These inflammatory mediators contribute in altering the vascular permeability, increasing mucous glycoprotein secretion, as well as stimulating the chemotaxis process, the activity of epithelial secretion and other mediators [17]. An intervention suppressing this inflammatory process, could have an important role in the resolution of AOM. Corticosteroids suppress the inflammation process by inhibiting the mediators and cytokines characteristic of AOM, the recruitment of leukocytes and monocyte-macrophages into affected areas, and the synthesis and/or release of numerous inflammatory mediators and cytokine, and also reducing vascular permeability [18].

Corticosteroids are produced in the adrenal cortex. Cortisol (glucocorticoids), one of the most common corticosteroids, is responsible for anti-inflammatory effects. The production of glucocorticoids is controlled by hypothalamus, pituitary, and adrenal (HPA) axis. Corticosteroid treatment may affect the production of natural corticosteroid by suppressing the HPA axis [19,20]. We have identified prednisolone is commonly used and safe in the treatment of inflammatory and autoimmune diseases in children. Prednisolone, a synthetic intermediate-acting glucocorticoid with a biological half-life of 12 to 36 hours, is commonly used in the treatment of inflammatory and autoimmune diseases in children. Although prednisolone has a lesser anti-inflammatory potency compared to other common corticosteroids (i.e. methylprednisolone, dexamethasone), but it has lesser growth effect which is one of the concerning issues in the disease management in paediatric population [19].

We will give prednisolone at a dose of 1 mg/kg to 2 mg/kg body weight based on age category, once daily for five days. As there is a wide therapeutic dose window for prednisolone, this will enable us to operationalise the dose as 10 mg/day for children aged six months less than two years; 20 mg/day for children aged two to five years; and 30 mg/day for children aged six to 12 years, simplifying both randomisation and dosage instructions. The current treatment for AOM does not include corticosteroids in the guidelines. Therefore, we determined the dose and duration of prednisolone based on the doses regularly used in the paediatric otitis media trials and regular dose for other inflammatory and infection diseases in children based on the international and national practice guidelines, such as bronchial asthma, juvenile rheumatoid arthritis, and acute bacterial meningitis [21-25]. The duration of corticosteroid use in otitis media trials varies between three to seven days [18, 26-28]. An animal study [29] using mice infected with *Streptococcus pneumoniae* and non-typeable *H. influenzae* (NTHi) bacteria demonstrated that most of AOM-related cytokines peaks at three to six hours after the infections (interleukin-6/IL-6, interleukin-1 alpha/IL-1 $\alpha$ , tumor necrosis factor alpha/TNF- $\alpha$ ) and at six hours to three days (interleukin-10/IL-10). In general, these cytokines will be progressively reduced between the fourth to sixth day of infection and the acute otitis media will be resolved after the sixth day [29]. Therefore, we will give the prednisolone for five days in order to boost the natural resolution mechanism in AOM cases and to minimize the potential harms of corticosteroid use even though 7-day duration is still regarded as short-term use.

A single daily dose is preferable over divided doses to prevent the hypothalamic-pituitary-adrenal (HPA) axis suppression. Prednisolone should be given in a single dose at 6 to 8 am in the morning to mimic the normal diurnal rhythm of cortisol production [19,20] and because it is also more convenient for children and parents in the study to just take a trial drug once a day.

### **Potential harms**

Despite the favourable effect of corticosteroids for inflammation, there are still several potential adverse effects related to its short-term use. A systematic review identified side effects of short-course of corticosteroids (less than two weeks) in children, such as gastrointestinal disturbances (i.e. vomiting, gastritis, nausea), behavioural changes (i.e. mood swings, nervousness), HPA axis suppression, increased blood pressure, hyperglycaemia, weight gain, and decreased bone mineralisation [30]. Even though there were more children experiencing these side effects compared to placebo, the included studies used a diverse of corticosteroids' types and duration, as well as the results were uncertain and include both important beneficial and harmful effects of

corticosteroid. Vomiting and behavioural disturbances (i.e. anxiety, aggressive behaviour) are the common side effects [30].

Regarding vomiting, there were three studies comparing prednisolone to placebo or control (other type of corticosteroids). A good quality RCT [31] included children aged 10 to 60 months with virus-induced wheezing who received a single dose of inhaled albuterol. These children then were randomly allocated to either prednisolone (10 mg oral prednisolone for children aged 2 years and younger; 20 mg for aged >2 years) group (n=343) or placebo (n=344). No significant differences on clinical outcomes (e.g. time to hospital discharge) or adverse effects between two groups were detected. There was one child from prednisolone group who vomited that required the discontinuation of the prednisolone [odds ratio (OR) 3.02 (95% confidence interval (CI) 0.12 to 74.33; p-value=0.50; number needed to harm (NNTH; number of children who are treated with prednisolone that will result in one additional event of side effects) = 34 children)] [31]. One study [32] on children aged one to 17 years with acute asthma presenting to the emergency department (ED). The children received a dose of inhaled albuterol and either a single dose of oral prednisone 2 mg/kg (n=41) or placebo (n=40). There was no a significant difference in the incidence of vomiting after taking the prednisone between the prednisone group (n=3; 7.3%) and the placebo group (n=1; 2.5%) [OR 3.08 (95% CI 0.31 to 30.92; p-value=0.34; NNH=21)] [32]. The same author with similar inclusion criteria [33] demonstrated a significant difference on the incidence of vomiting between children who received single dose prednisone 2 mg/kg/day (n=10/66) and nebulised dexamethasone 1.5 mg/kg (n=0/62), however the confidence interval was very wide that included a high number of NNTH (if we treat more than 50 children with prednisone, then we will expect one additional event of vomiting) [OR 23.23 (95% CI 1.33 to 405.54; p-value=0.03; NNH=7)] [33].

Regarding behavioural changes, one RCT [34] randomly allocated children aged two to 16 years with acute exacerbation of mild persistent asthma to receive either oral prednisone/prednisolone high dose (2 mg/kg/day) or low dose (1 mg/kg/day) for five days. There were significant differences in observed adverse events between high-dose and low-dose groups in regard to anxiety (9/43 vs 2/43, respectively) [OR 5.43 (95% CI 1.10 to 26.83; p-value=0.04; NNTH=7)] and aggressive behaviour (9/43 vs 0/43) [OR 23.96 (95% CI 1.35 to 426.33; p-value=0.03; NNTH=5)]. The wide of intervals demonstrated a wide variance in the number of children needed to treat to expect one additional adverse event. There were no significant differences in other unfavourable effects (i.e. facial fullness and erythema, abdominal pain, diarrhea, euphoria, depression, and hyperactive) [34]. Another RCT [35] included children aged two to 15 years with acute exacerbation of asthma who were randomly allocated to receive oral prednisolone 1 mg/kg/day for three days (5-day group) vs same dose of prednisolone for three days (3-day group). There were no significant differences in regard to the incidence of rash and behavioural disturbance (e.g. angriness, aggressiveness, crankiness, irritability) between the two groups [35].

An RCT of the use of prednisolone for pediatric AOM reported no significant differences between children who received oral prednisolone 2 mg/kg/day for five days and placebo group who experienced moderate side effects (e.g. drowsiness, nervousness, diaper rash, dry mouth) [18]. This study also demonstrated that there was no correlation between the use of corticosteroid and the persistence or the emergence of viral infections [18]. Other potential side effects correlated with the use of corticosteroids are fluid retention and headache [18,30].

**Based on these trials, we consider 5-day duration of prednisolone for this study is appropriate and safe for children.**

### ***Clinical trial of corticosteroids for acute otitis media in children***

Evidence has demonstrated insufficient benefits and harms of corticosteroids. An RCT demonstrated that corticosteroid reduced the duration of ear discharge in AOM children with ventilation tubes [26]. Another RCT demonstrated a temporary resolution of middle ear effusion after five days of corticosteroid treatment [18]. In a systematic review of randomised placebo-controlled trials (RCTs) of steroids for AOM, only two small trials [18,27,36] (very low to low quality) indicated corticosteroids could be useful in this condition. However, our confidence in the results is low, due to small sample size and very wide confidence intervals around the observed results. This insufficient evidence creates a research gap in the management of AOM, particularly in non-severe cases, where antibiotics are not required. Therefore, we propose an adequately powered clinical trial to address this uncertainty.

We will conduct a large, parallel, pragmatic, multicentre, stratified, double-blind, randomised, placebo-controlled trial with the allocation ratio 1:1 to test the effectiveness of corticosteroids for 760 children with AOM including 60 children for a tympanometric mechanistic sub-study and pilot study, described further in this protocol. As a comparator to prednisolone, we will use a placebo for the following advantages: (1) it is the most accurate test in assessing the efficacy of a treatment; (2) it will show the true additional benefits and/or harms of the prednisolone; and (3) it is crucial when the outcome is assessed using subjective measurements. The primary objective and outcome of this proposed trial is to assess the effectiveness of corticosteroids as a monotherapy in children with mild AOM, and as an addition to antibiotics in children with severe AOM, on ear pain at three days after randomisation using visual analogue scale (VAS). The secondary outcomes include ear pain at other time points, total duration and severity of pain, adverse effects, complications of AOM (e.g. perforation of tympanic membrane, mastoiditis), and AOM recurrence.

#### **1.1.3 Rationale for pilot study**

Prior to our main study, we will conduct a pilot study, described in this protocol. This study will mimic the main study in terms of its process and procedures, but on a smaller scale. However, due to budget constraints, we will conduct a pilot study as a pragmatic, randomised, open-label, single-blind study. We will blind outcome assessors (i.e. physicians and tympanometry technicians), so they will not aware of the allocation of the intervention.

The main study will involve many participating physicians and healthcare facilities across Jakarta, Bekasi, and Depok, most of whom have not been involved in a clinical trial before, will have a long follow-up period up to three months, and will utilise a symptom diary and a specific translated instrument to assess the severity of symptoms (acute otitis media – severity of symptom scale or AOM-SOS) which is not widely recognised by physicians in Indonesia. Therefore, this pilot study is crucial to test the feasibility of the main study, including the characteristics of our main study design, all the study processes and procedures (e.g. the recruitment, stratification, randomisation, outcome measurement), and other operational strategies in our proposed main study.

## 1.2 Objectives

The first objective of our pilot study is to assess the overall process and procedures of the main study, as follows: (1) the recruitment criteria; (2) stratification and randomisation processes; (3) outcome measures using validated and customised tools (e.g. visual analogue scale/VAS, Acute Otitis Media – Severity of Symptoms Scale/AOM-SOS, case report forms/CRFs, symptom diary); (4) identification of any potential practical and operational issues that may appear in the main study which will require re-structuration of the planned methods and procedures after commencing this pilot study; and (5) verification of sample size calculation for main study.

Our second objective is to conduct a mechanistic explanatory study using tympanometry. It aims to assess the efficacy of corticosteroids in improving the resolution of middle ear effusion in AOM.

## CHAPTER 2 – METHODS

### 2.1 Trial design

This study is a pilot of a parallel, pragmatic, stratified, randomised, open-label, single-blind controlled trial of corticosteroids, as monotherapy for mild AOM, and in addition to individually prescribed antibiotics for severe AOM. In the main study, we will stratify eligible children based on the clinical specialty (primary care or secondary/tertiary care) and severity of AOM (mild or severe). However, for this pilot study, we only include ear-nose-throat-specialists (ENTs) who work at tertiary centres for the convenience of the implementation of the mechanistic sub-study as tympanometry is only available at the hospitals (tertiary centres). Therefore, we will stratify the children based on their AOM severity and then will randomly allocate to corticosteroid (prednisolone) or control (usual care without prednisolone) (Figure 1) with the allocation ratio of 1:1. Because it is an open-label study, the parents/caregivers and an appointed nurse who will perform the randomisation will be aware of treatment allocation, whilst the clinicians and tympanometry technicians will remain unaware of the treatment.

### 2.2 Participants, interventions, and outcomes

#### 2.2.1 Study setting

Prior to this study, we conducted a feasibility study to survey the current management of AOM in children in three cities in Indonesia and to identify the willingness of physicians to participate in our proposed clinical trial of corticosteroids for AOM in children. Based on clinical scenarios, there were sufficient number of physicians who would prescribe corticosteroids for AOM. There were 171 physicians from 87 primary/secondary to tertiary centres (public and private) in DKI Jakarta, Depok, and Bekasi who were willing to participate in our proposed main study. However, we will only pilot this study at seven public and private hospitals in Jakarta and Bekasi: (1) [name] Hospital; (2) Persahabatan Hospital; (3) Gatot Subroto Army Hospital; (4) Antam Medika Hospital; (5) Cempaka Putih Islamic Hospital; (6) Proklamasi ENT Hospital; and (7) Hermina Bekasi Hospital.

#### 2.2.2 Eligibility criteria

##### 2.2.2.1 Inclusion criteria

We will include 60 children aged six months to 12 years old with AOM, defined as current onset (48 to 72 hours) of AOM-relevant symptoms (e.g. earache, ear tugging/rubbing or irritability in non-verbal children). If it is feasible, otoscopic findings of middle ear effusion (e.g. bulged tympanic membrane, limited or absent mobility of the tympanic membrane, air fluid level, ear discharge) and acute inflammation (e.g. erythema) will confirm the diagnosis.

##### 2.2.2.2 Exclusion criteria

We will exclude children:

1. with major and severe medical conditions (e.g. heart diseases, kidney failure)
2. who are immunocompromised (e.g. HIV, children receiving cancer treatment)
3. with congenital malformations and/or syndromes (e.g. cleft palate, Down's syndrome)
4. with ear ventilation tube(s)

5. exposed to persons with varicella (chicken pox) or active Zoster infection in the past three weeks without prior varicella immunisation or infection
6. who have high risk of strongyloidiasis infections with symptoms and signs of unexplained eosinophilia, skin reaction due to larvae penetration into the skin (e.g. inflammation, oedema, petechiae, severe pruritus), particularly on the feet regions, pulmonary (e.g. dry cough, throat irritation, dyspnoea, wheezing, haemoptysis, repeated episodes of fever and mild pneumonitis), or gastrointestinal symptoms (e.g. upper abdominal pain, diarrhea, anorexia, nausea, epigastric pain, malabsorption, and vomiting)
7. who have taken systemic (i.e. oral, injection) or topical steroids in the preceeding four weeks
8. who have taken antibiotics in the preceeding two weeks
9. who are hypersensitive to prednisolone or prednisone, or other corticosteroids

### **2.2.3 Interventions**

Children in the mild AOM group will be randomly allocated to receive either a single dose of prednisolone tablets daily for five days as an addition to expectant observation or expectant observation alone (without prednisolone). At the baseline visit, the participating physicians will inform the parents/caregivers to closely observe the children for 48 hours without immediate antibiotic treatment.

Children in the severe AOM group will be randomly allocated to receive either a single dose of prednisolone tablets daily for five days as an addition to antibiotics according to physicians' preferences or antibiotic alone (without prednisolone). Antibiotic treatment is commonly prescribed for AOM with severe symptoms. The information regarding the antibiotics (e.g. antibiotic type, dose, duration) will be recorded in the case report forms (CRFs).

#### **2.2.3.1 Prednisolone and control group**

##### ***Prednisolone group***

Prednisolone tablets will be given in the intervention groups in both mild and severe groups. It is given at a dose of 1 mg/kg to 2 mg/kg body weight, once daily for five days. The pharmacist will crush the tablets, mix them with sweeteners, and pack them in a daily paper-pack. It should be given in a single dose at 6 to 8 am in the morning to mimic the normal diurnal rhythm of cortisol production [19,20]. Participating physicians will advise the parents to give the prednisolone at about the same time each day as a daily routine for children which will also help parents to remember.

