| Intervention(s)                               | Intervention Name:

 
Active intervention: Prednisolone tablet
 
Active comparator: None
 
 Intervention Description:

 
Prednisolone tablet with doses based on range of age for five days: 
 
6 months – <2 years: 10 mg/day
 
2 – <6 years: 20 mg/day
 
6 – 12 years: 30 mg/day
 
 
 
None
 
                                                                                                                                                                                                                                                                                                      |
| Key Inclusion and Exclusion Criteria          | Ages eligible for study: 6 months to 12 years
Sexes eligible for study: both males and females
Accepts healthy volunteers: no
Inclusion criteria:

 
children (6 months – 12 years) with acute otitis media, defined as a current onset within 48 hours of ear-related symptoms (e.g. ear pain, ear tugging/rubbing or irritability) and if possible to assess, otoscopic findings of acute inflammation (e.g. erythema) and middle ear effusion (e.g. bulging, air-fluid level)
 
 Exclusion criteria:

 
children with major and severe medical conditions (e.g. heart failure, kidney failure)
 
immunocompromised children (e.g. HIV, children receiving cancer treatment)
 
 |

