### ***Allocation concealment mechanism and implementation***

The information of the eligibility and stratification which is provided by the participating physicians will help the appointed nurses to obtain the information from the randomisation website, whether the children will be allocated to the prednisolone or control group, identified by the 2-digit patient ID numbers. During the consultation, the physician will prescribe study medication for every subject with the dose based on the patient age and insert the prescription in the CRF folder. The nurse who performs the randomisation will give the prescription to the subjects who are allocated to the intervention group (prednisolone group). The subject then will give the prescription to the pharmacy, where the pharmacist will prepare the prednisolone by crushing the tablets, mixing them with sweeteners, packing the prednisolone mixed powder in a daily individual paper-pack for five days, and dispense these to the subjects along with instructions for preparation. The pharmacist will record the dispensing on the form provided by the study for this purpose.

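### Section 2.2.3.1 gives the prednisolone dose only as 1–2 mg/kg, while the protocol doses by age band elsewhere, and the age-band doses cannot give 1–2 mg/kg to every child who may be enrolled

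*Protocol*

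**What the plan says.** The protocol describes the dose in four places.

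- **Section 2.2.3.1, Prednisolone group** (the intervention section): "It is given at a dose of 1 mg/kg to 2 mg/kg body weight, once daily for five days". It gives no age bands and does not refer to any.
- **Section 1.1.2, Prednisolone** (the rationale): "We will give prednisolone at a dose of 1 mg/kg to 2 mg/kg body weight based on age category, once daily for five days". The next sentence turns this into fixed amounts: 10 mg daily below the age of two, then "20 mg/day for children aged two to five years; and 30 mg/day for children aged six to 12 years". The reasons given are a wide dose window and simpler randomisation and instructions.
- **WHO Trial Registration Data set**: "Prednisolone tablet with doses based on range of age for five days", with the same three bands. The highest reads "6 – 12 years: 30 mg/day".
- **Section 2.3.1, Allocation concealment mechanism and implementation** (the prescribing step): "the physician will prescribe study medication for every subject with the dose based on the patient age".

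On who may enter, section 2.2.2.1 says: "We will include 60 children aged six months to 12 years old with AOM". Sections 2.2.2.1 and 2.2.2.2 set no weight limit. Table 1 in 2.2.5 lists weight among the baseline measurements but does not link it to the dose.

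**The concern.** The section a reader would consult for the intervention gives a weight-based range, whereas the step that produces the prescription uses age. The rationale joins the two by treating the fixed amounts as a way of giving 1–2 mg/kg. If that link held for every child, the difference would be one of wording only. If it fails for some children, the protocol states a property of the dose that the design does not deliver, and it does so in the operative section.

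Two things are at stake. First, the description of what was given would be inaccurate for some children, and this pilot is meant to rehearse the procedures of a 760-child main study. Second, part of the safety discussion in 1.1.2 is expressed per kilogram. It cites a comparison of 2 with 1 mg/kg/day that found anxiety in 9/43 v 2/43 children and aggressive behaviour in 9/43 v 0/43.

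**Working it through.** **Inputs from the protocol.** Stated range: 1–2 mg/kg once daily (1.1.2 and 2.2.3.1). Fixed daily doses: 10 mg from 6 months to under 2 years, 20 mg from 2 to under 6 years, 30 mg from 6 to 12 years (registration data set; the rationale's bands are the same). Weights by age: not given anywhere.

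**Step 1. Weights at which each band gives 1–2 mg/kg.** Dose per kg = D / w, where D is the fixed dose in mg and w the weight in kg. Requiring 1 ≤ D / w ≤ 2 gives D/2 ≤ w ≤ D.

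| Age band | D | In range for weights of |
|---|---|---|
| 6 months to <2 years | 10 mg | 5–10 kg |
| 2 to <6 years | 20 mg | 10–20 kg |
| 6–12 years | 30 mg | 15–30 kg |

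**Step 2. The second birthday, using the protocol's figures alone.** Just before it the dose is 10/w, in range for 5–10 kg. Just after it the dose is 20/w, in range for 10–20 kg. The two intervals share one point, w = 10 kg.

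- If w > 10, then 10/w < 1 just before the birthday.
- If w < 10, then 20/w > 2 just after it.

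Suppose the weight distribution is the same just before and just after the birthday. The share below 1 mg/kg just before and the share above 2 mg/kg just after then add to 1, because they are the shares above and below 10 kg. Illustration with assumed normal weights and a coefficient of variation of 8–15%:

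| Assumed mean weight at age 2 | Below 1 mg/kg just before | Above 2 mg/kg just after |
|---|---|---|
| 9 kg | 8–23% | 77–92% |
| 11 kg | 73–87% | 13–27% |

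**Step 3. The sixth birthday.** 20 mg is in range for 10–20 kg and 30 mg for 15–30 kg, so the intervals overlap at 15–20 kg. This boundary does not force children out of range.

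**Step 4. The top of the age range.** 30/w ≥ 1 requires w ≤ 30 kg for every child up to and including age 12. Nothing in the eligibility criteria ensures this.

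**Step 5. Illustrative departures.** All weights here are assumptions.

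- Under 2 years, 11–13 kg: 10/11 = 0.91 down to 10/13 = 0.77 mg/kg.
- 2 to <6 years, 9 kg: 20/9 = 2.22 mg/kg; 22–25 kg: 20/22 = 0.91 down to 20/25 = 0.80 mg/kg.
- 6–12 years, 35–50 kg: 30/35 = 0.86 down to 30/50 = 0.60 mg/kg.
- Share of 12-year-olds below 1 mg/kg: from 5% (mean 25 kg, coefficient of variation 12%) to 98% (mean 40 kg, 12%).

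**Step 6. Do the two rules conflict for one child?** Sometimes.

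- A 15 kg child aged 2 to 5 gets 20 mg by age, which lies within the 15–30 mg that 2.2.3.1 allows. Both statements are met.
- A 12 kg child just under 2 gets 10 mg by age, which lies outside the 12–24 mg that 2.2.3.1 allows. Both cannot be met.

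**The case against.** The strongest reply is that the protocol already connects its statements. The rationale says that the per-kilogram dose is applied by age category and gives a reason for fixed amounts. The registration data set has the same bands, and the prescribing step doses by age. Three places thus agree on one rule, and 2.2.3.1 can be read as a shortened restatement. Age banding with a stated reason is a legitimate choice in a pragmatic pilot.

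Most of this stands. A reader might infer from 2.2.3.1 that the intervention is undefined, or that two physicians would generally prescribe differently for the same child. The documents do not support that: the prescribing step and the registered bands yield a single dose, and for many children it also satisfies 2.2.3.1.

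A reader might also infer that the safety case rests entirely on mg/kg. It does not. The largest trial cited under Potential harms (343 v 344 children) used fixed doses of 10 and 20 mg split at about age 2, close to the two lower bands here. That trial covered ages 10 to 60 months, so it does not reach the 30 mg band. In addition, most of the illustrated departures fall below 1 mg/kg, and the cited comparison of 2 with 1 mg/kg/day raises no concern about those.

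What the reply does not rescue is the stated equivalence. A wide dose window may justify fixed doses, but it does not make them equal to 1–2 mg/kg for every child.

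**Conclusion.** The point holds in a limited form. Section 2.2.3.1 omits the age bands used elsewhere, and those bands cannot keep every child who may be enrolled within 1–2 mg/kg. The result at the second birthday follows from the protocol's own figures and needs only the mild assumption that children of about two do not all weigh 10 kg. The failure at the top of the age range needs only a child of 12 or under who weighs more than 30 kg.

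A reader might go further and conclude that the bands generally miss the range. The documents do not support that: a child of 5–10, 10–20 or 15–30 kg in the respective band is in range, and many will be. The number outside cannot be fixed without weight data, as the 5% to 98% span at age 12 shows. Among the 60 children it also depends on the ages recruited.

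The sample size is unaffected, since dose does not enter the calculation of 22 per group. This is a correction to the wording of the intervention. It implies no view on which dose or dosing rule is right.

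**What to change.** The investigators should reconcile the registration data set, section 1.1.2, section 2.2.3.1 and section 2.3.1 to one dosing statement of their choosing, and carry it into the prescription and the drug dispensing form. If the age bands stay, the statement that they give 1–2 mg/kg should be corrected or qualified, for example by naming the weights for which it is true.

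As an optional addition, the mg/kg actually given can be summarised from the baseline weight already collected. Its absence is not a defect.

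The cost is a wording change handled under section 2.6.2, plus one derived variable if the optional summary is wanted. No new data are needed, and neither the sample size nor the planned comparisons change.
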